Recently, another modality, namely pulsed ultrasound with low-intensity has been found useful in the acute management of patients with TKA. The therapy was also not stated as a contraindication for the patient with metal implants.^[30]^ However to date, this finding was reported only in one study.^[31]^ The researchers^[31]^ investigated the effect of combining low-intensity pulsed ultrasound with cryotherapy on recovery of joint function and the inflammatory index C-reactive protein in female patients with TKA. No adverse effects were reported, indicating that the modality is safe to be used on patients with TKA. The researchers found that patients who received low-intensity pulsed ultrasound in combination with cryotherapy shown greater improvement in the recovery of joint function, knee range of motion and reduction of inflammation compared to patients who received cryotherapy or low-intensity pulsed ultrasound alone. However, the study did not look into the effect of the adjunct modality on the recovery of all physical impairments which also include pain, swelling and quadriceps weakness during early stage post-TKA and how these influence the recovery of function in the post-acute phases. Further resources for acute management after TKA are needed to improve acute pain control^[32]^ and future research on the effect of impairment-targeted interventions in acute hospital and inpatient rehabilitation setting is recommended.^[33]^

The objective of this quasi-experimental assessor-blinded study is to evaluate the effects of low-intensity pulsed ultrasound as an adjunct to conventional physiotherapy on the recovery of physical impairments, functional performance and quality of life in patients with TKA. This study also intends to assess the influence of the recovery of physical impairments following Pulsed ultrasound-added physiotherapy on functional performance and quality of life of patients with TKA.

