### Assessment of outcomes

2.6

Two days prior to TKA surgery, a researcher will verbally invite potential participants and briefly explain the purpose and procedure of the study before distributing the information sheets to them. At post-operative day 2, the participants will be further screened for eligibility and an informed consent will be obtained from patients who are eligible and agreed to participate. Once recruited, the socio-demography, information of height, weight and body mass index (BMI) of the participants will be recorded. The dose of analgesic medication used will be obtained from patients’ medical record (in-patient) and based on the patients’ report (out-patient).

All participants will undergo baseline assessments before allocated alternately into the two groups at post-operative day 2 for physical impairments, and quality of life following removal of drainage tubes and discontinuation of patient-control analgesia. Baseline assessment for functional performance will be performed at week 1 after the surgery.

Assessment of outcomes following intervention will be conducted at 4 assessment time points which are at week 1, 4, and 12 following TKA surgery and at 3-month follow-up (6 months after the surgery). Outcomes on physical impairments will be assessed at the end of week 1, 4, and 12 following the surgery and at 3-month follow-up. Whereas, outcome on the functional performance will be assessed at week 4 and 12 after the surgery and at 3-month follow-up. Finally, the interventions’ outcome on quality of life of the participants will be assessed at 3-month follow-up or 6-month post-surgery.

A trained physiotherapist who is blinded to the participants’ group allocation is responsible to conduct and record all assessments. To avoid recall bias, the recorded measurements of patient's pre-intervention status will not be accessible to others during the patient's post-intervention assessment.

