### Data analysis

2.8

All data will be analyzed by the researcher using the statistical package for the social sciences (SPSS) 20.0 software, IBM Corporation. If missing data are identified, intention-to-treat will be used to ensure unbiased estimates of treatment effects between the two groups, and all participants who are recruited at baseline will be included in the outcome analysis.^[47]^

The characteristics of the participants will be presented in descriptive statistics. Mixed model ANOVA will be used to evaluate time, group and interaction effects of the interventions on participants’ pain, knee swelling, knee range of motion and quadriceps strength, as well as on the patients’ functional performance and quality of life. Further, multiple regression will be used to determine how much do recovery in physical impairments following low-intensity pulsed ultrasound as an adjunct to conventional physiotherapy influence the functional performance and quality of life of the patients. The level of significance is set as *P* < .05.

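### As worded, the regression of function and quality of life on impairment recovery supports association only; it cannot attribute gains to ultrasound-related recovery

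*Protocol article*

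**What the plan says.** Protocol article, section 2.8 (Data analysis), plans two analyses. The first carries the group comparison: "Mixed model ANOVA will be used to evaluate time, group and interaction effects of the interventions", applied to every impairment and to function and quality of life. The second is the one at issue: "multiple regression will be used to determine how much do recovery in physical impairments following low-intensity pulsed ultrasound as an adjunct to conventional physiotherapy". What this recovery is asked to explain comes at the end of the same sentence, in causal terms: "influence the functional performance and quality of life of the patients".

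The last paragraph of the Introduction sets the matching aim, to "assess the influence of the recovery of physical impairments following Pulsed ultrasound-added physiotherapy on functional performance and quality of life of patients with TKA". The Discussion (section 3) repeats it. All three places tie the predictor to recovery in the ultrasound-added programme, and none mentions control-arm recovery for this analysis.

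Section 2.6 gives the schedule. For impairments, after a baseline on post-operative day 2: "Outcomes on physical impairments will be assessed at the end of week 1, 4, and 12 following the surgery and at 3-month follow-up". For function, after a baseline at week 1: "outcome on the functional performance will be assessed at week 4 and 12 after the surgery and at 3-month follow-up". After a day-2 baseline, "quality of life of the participants will be assessed at 3-month follow-up or 6-month post-surgery".

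**The concern.** The question is worded causally and concerns one treatment programme. The tool named for it is a plain multiple regression of outcome on recovery. Patients who heal well tend to do so on every measure, so impairment recovery and function will correlate after surgery with or without ultrasound. A slope estimated within the ultrasound arm, or in all patients without a group term, mixes ordinary post-operative recovery, shared prognosis and any ultrasound effect, and cannot separate them.

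For quality of life there is also overlap in content: the EQ-5D has its own pain/discomfort and mobility dimensions (section 2.5), so pain recovery is partly on both sides of the equation.

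At stake is the explanatory conclusion. A significant slope could be presented as evidence that recovery brought about by ultrasound improves function or quality of life, when the same slope would be expected if ultrasound did nothing.

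**Working it through.** The protocol gives no sample size, effect size or power for this regression, so there is no figure to reproduce. Section 2.7 leaves the main sample size to a pilot with 10 per group. Only alpha = 0.05 comes from the document; I take it as two-sided. The rest is assumed for illustration.

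**Model (SD units).** Group g = 0 or 1; shared prognostic factor u; impairment recovery m = a·g + l·u + error; function y = b·m + l·u + error. Errors are scaled so that m has variance 1 within an arm. Here a is the ultrasound effect on recovery, b the true effect of recovery on function, and l the loading of shared prognosis.

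**Expected slope within the ultrasound arm.** Cov(m, y)/Var(m) = b + l². The effect a does not appear, because g is constant within an arm.
- b = 0, l = 0.7: 0 + 0.49 = 0.49.
- b = 0.5, l = 0: 0.50.

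**Pooled without a group term.** The slope is b + l²/(1 + a²/4). With b = 0, l = 0.7, a = 0.5: 0.49/1.0625 = 0.46, against 0.49 at a = 0. This barely separates the two cases either.

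**Simulation, 3000 trials per scenario, ultrasound-arm regression.** The three values in a cell are for 20, 30 and 50 per arm.

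| a | b | l | Mean slope | Significant (%) |
|---|---|---|---|---|
| 0 | 0 | 0.7 | 0.495, 0.496, 0.488 | 63.4, 81.9, 95.9 |
| 0 | 0.5 | 0 | 0.500, 0.501, 0.501 | 52.4, 72.0, 91.1 |
| 0.5 | 0 | 0.7 | 0.485, 0.487, 0.491 | 62.2, 80.2, 96.4 |
| 0.5 | 0.5 | 0 | 0.504, 0.500, 0.504 | 53.7, 72.5, 91.8 |

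Rows that differ only in whether shared prognosis or a real effect produces the slope look alike. So do rows that differ in whether ultrasound works.

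**Check by Fisher's z for a single correlation.** P(significant) = Φ(atanh(r)·√(n − 3) − 1.96).
- r = 0.5, n = 20: 0.549 × 4.123 − 1.96 = 0.305, giving 0.62. At n = 40: 0.92.
- r = 0.3: 0.25 at n = 20 and 0.47 at n = 40.

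This concerns one predictor, not the full multiple regression, so it shows order of magnitude only.

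**What a group term adds.** Take the group effect on recovery times the group-adjusted slope, that is a(b + l²) on average. With a = 0 it is 0 (simulated −0.003 to 0.002), so the false signal disappears when ultrasound does not change recovery. With a = b = 0.5 and l = 0 it is 0.25, which is correct. With a = 0.5, b = 0, l = 0.7 it is 0.5 × 0.49 = 0.245 (simulated 0.244 to 0.252), although the true indirect effect is 0. A group term is needed but does not remove confounding between recovery and outcome.

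**The case against.** The strongest reply is that one sentence in an article is not a model specification. Covariates, time points and the analysis set of a secondary regression are commonly left to a full protocol or analysis plan that is not shown here. That stands for two stronger readings that a reader might infer.

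- **That the regression has no time ordering.** The sentence is silent, and silence is not a choice. The schedule in section 2.6 permits lagged models. Quality of life after baseline is measured only at 6 months, so recovery to week 12 would precede it. The Introduction, in describing the gap left by the earlier study, speaks of early impairments bearing on later function.
- **That a group term is excluded, or that mediation by ultrasound-induced recovery is the declared aim.** The document does neither. It speaks of recovery after the ultrasound-added programme and never names mediation or an indirect effect. A within-arm question about association is legitimate and regression can answer it.

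It is also fair that the mixed ANOVA would stand beside the regression. In the simulated cases with no ultrasound effect, a simple group comparison was significant in only about 5% of trials, so a careful reader would usually see no group difference.

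What the reply does not remove is the pairing itself. A causal question tied to one programme, given in three places, is matched to a regression with no stated control comparison. The mixed ANOVA tests group effects on each outcome separately and does not link impairment recovery to function. An analysis plan that followed this wording would carry the mismatch forward.

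**Conclusion.** The point holds in limited form. As worded, the regression can show that recovery and later status are associated after knee arthroplasty. It cannot show that gains in function or quality of life are due to ultrasound-related recovery, because the slope is about the same (0.49 to 0.50 in the illustration) whether ultrasound has an effect or not. The significance rates of 63% to 96% under pure shared prognosis rest on the assumed loading of 0.7 and on 20 to 50 per arm. With weaker correlation they fall, to 25% for r = 0.3 and n = 20. None of these inputs is in the protocol. That the slope carries no information on the ultrasound effect does not depend on the sample size.

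This is an explanatory aim. The primary group comparison of impairments is untouched. The matter is worth correcting because the correction is cheap and changes what the trial may claim.

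**What to change.** Either of two changes would do.

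1. **Keep the causal question and give it a suitable model.** Fit the regression in both arms with a group term. Use impairment change from day 2 to an earlier visit, for example week 4, to predict a later outcome: function at week 12 or 6 months, quality of life at 6 months. Adjust for day-2 impairment, age and BMI, and for day-2 quality of life where that is the outcome. Function has no pre-treatment value to adjust for, since its baseline is taken at week 1 and ultrasound starts on day 2. Report any indirect effect as exploratory, with a bootstrap 95% confidence interval and an explicit statement that unmeasured confounding between impairment recovery and outcome may bias it.
2. **Keep the simple regression and change the claim.** Replace the wording of influence by association in the Introduction, section 2.8 and the Discussion, and drop the attribution to ultrasound.

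All measurements needed are already scheduled. The first option costs a modest extra analysis, and its intervals will be wide. The second costs only wording.

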### Ethics and dissemination

2.9

The study received ethical approval from Research Ethics Committee of the Universiti Kebangsaan Malaysia Medical Centre (study code NN-2018-111). Each participant can withdraw anytime during the study without giving any explanation. All personal information and data provided by participants will be kept confidential. Investigators in this study will have access to the final trial dataset. The findings of this study will be published in a peer-reviewed journal.

## Discussion

3

This study will compare the changes in physical impairments between patients with TKA who received low-intensity pulsed ultrasound as an adjunct to conventional physiotherapy and patients who received conventional physiotherapy only. Previous study^[31]^ did not specifically look at the effect of the interventions on the recovery of other important physical impairments such as pain, swelling and quadriceps weakness after TKA. Therefore, this study will provide knowledge regarding the effects of adding low-intensity pulsed ultrasound in post-operative rehabilitation into conventional physiotherapy on recovery of more physical impairments which are pain, swelling, knee range of motion, and quadriceps strength of patients with TKA.

Further, results of the secondary outcomes will provide information on the recovery of the functional performance and quality of life between patients with TKA who received low-intensity pulsed ultrasound and patients who did not receive the treatment. Well-targeted post-operative rehabilitation intervention can further improve the patients’ recovery, and eventually enhance the patients’ functional performance and quality of life. A study stated that pain and lower limbs function are important predictors for the improvement in quality of life of patients after TKA.^[48]^ Results of this study will be further analyzed to assess the influence of the recovery of physical impairments following pulsed ultrasound-added conventional physiotherapy on functional performance and quality of life of patients with TKA.

It is our hope to be able to determine the benefits of adding low-intensity pulsed ultrasound into conventional physiotherapy in enhancing the recovery of physical functions in patients with TKA. Findings from this study can therefore be used as a reference for designing future studies and in establishing evidence regarding the use of low-intensity pulsed ultrasound on population after TKA surgery.
